## Abstract

**Background:**

Some probiotics appear to improve athletic performance, endurance, and recovery after intense exercise. Other formulations may provide performance-related benefits via immune and gastrointestinal functions in athletic individuals. However, few formulations have been studied for both types of effects among non-elite athletes. The primary objective of this study is to assess the ergogenic effects of a probiotic on high-intensity endurance running performance in non-elite runners. Secondary objectives include assessment of perceived exertion, blood chemistry, immune and stress biomarkers, cold and flu symptoms, and gastrointestinal health after the probiotic intervention.

**Methods:**

This 9-week randomized, placebo-controlled, double-blind, parallel trial will assess the ergogenic effects of a probiotic (5 billion colony-forming units/day, for 6 weeks) in healthy, non-elite runners (*N*=32; 18–45 years). Participants will be monitored via daily and weekly questionnaires during the 2-week pre-baseline, 6-week intervention, and 1-week washout. Questionnaires will inquire about activity, muscle soreness, gastrointestinal symptoms, cold and flu symptoms, stool form and frequency, and adverse events. During the pre-baseline visit, maximal oxygen uptake (V̇O_2_ max) is assessed to set appropriate individualized workload settings for the treadmill time-to-exhaustion endurance tests. These time-to-exhaustion endurance running tests will be completed at an intensity of 85% VO_2_max at baseline and final visits. During these tests, self-perceived exercise effort will be rated via the Borg Rating of Perceived Exertion scale and finger sticks assessing capillary blood glucose and lactate concentrations will be collected every 3 min. Additional questionnaires will assess diet and motivation to exercise. Body composition will be assessed using air displacement plethysmography at the baseline and final visits. Hypotheses will be tested using two-sided tests, and a linear model and with a type I error rate of *α*=0.05. Primary and secondary outcomes will be tested by comparing results between the intervention groups, adjusting for baseline values.

**Discussion:**

These results will build evidence documenting the role of probiotics on running endurance performance and physiological responses to exercise in non-elite athletes. Understanding the potential mechanisms of probiotic effects and how they mitigate the intestinal or immune discomforts caused by running could provide additional strategy means to help runners improve their performance.

**Trial registration number:**

ClinicalTrials.govNCT04588142. Posted on October 19, 2020.

Protocol version: July 2, 2021, version 1.2

## Introduction

### Background and rationale

Running is the most popular sport worldwide that confers numerous health benefits [1]. Intense exercise can trigger a stress reaction that negatively impacts the immune system, causes gastrointestinal discomfort, and compromises performance [2]. To mitigate stress-induced symptoms related to exercise and to improve endurance performance, athletes often turn to nutritional supplements, such as probiotics. The International Olympic Committee defined probiotics as live microorganisms that were “associated with a range of potential benefits to gut health, as well as modulation of immune function” [3]. In addition, the Food and Agriculture Organization of the United Nations and the WHO (FAO/WHO) defines probiotics as “live microorganisms that, when administered in adequate amounts, confer a health benefit on the host” [4]. Probiotics positively influence the immune system after intense exercise by decreasing both the intensity of respiratory symptoms and the risk of developing a respiratory infection, and by reducing gastrointestinal symptoms potentially through modulation of the gut microbiota, increased production of beneficial metabolites, and improvements in intestinal barrier function [5, 6]. Theoretically, through the modulation of training-induced symptoms, probiotics could enhance athletes’ ability to train at high intensities while avoiding training time interruptions, thereby improving performance [5]. Most studies investigating the effects of probiotics on gastrointestinal and immune symptoms associated with intense exercising yield conflicting results [7]. For example, Shing et al. administered 45 billion colony-forming units (CFU, a term used to describe the number of viable microorganisms in a probiotic supplement) of *Lactobacillus, Bifidobacterium*, and *Streptococcus* to male non-elite runners for 4 weeks; a “small to moderate” improvement on gastrointestinal permeability was detected, with no influence on inflammatory markers [8]. In contrast, a 4-week *Lactobacillus* (20 billion CFU) intervention in fatigued athletes restored the T-cell production of INF-γ (a pro-inflammatory cytokine mediating anti-viral and anti-bacterial immunity), to levels seen in healthy athletes [9]. Moreover, when administered for 14 weeks, a *Lactobacillus* probiotic (20 billion CFU) intervention maintained concentrations of salivary secretory immunoglobulin A (sIgA), a marker of mucosal immune function, and reduced the total number of upper respiratory infection days among elite athletes [10, 11].

Recent studies suggest that probiotics, namely *Lactobacillus*, could improve athletic performance. These ergogenic effects were detected in athletes with various sport specializations, including runners [7, 8, 12–15]. Huang et al. observed a dose-dependent improvement in time-to-exhaustion during treadmill testing in non-elite athletes (*N*=54, age 20–30 years) who received a *Lactobacillus* probiotic (30 billion CFU and 90 billion CFU) for 6 weeks [12, 13]. Similarly, time-to-exhaustion was improved in a running protocol after administering a probiotic formulation composed of *Lactobacillus*, *Bifidobacterium*, and *Streptococcus* to male non-elite runners (*N*=10, age 25–29 years) for 4 weeks [8]. Possible endurance-enhancing mechanisms include alteration of the gut microbiota which could impact muscle substrate use, increased glucose availability and enhanced antioxidant defense to combat exercise-induced oxidative stress [13]. In contrast, in elite athletes, there was no improvement in running endurance after a 14-week *Lactobacillus* intervention (*N*=50, age 20–25 years) compared to placebo [11].

Interpretation of the performance findings related to probiotics may be clouded by variations in training status of runners enrolled in the research. Some elite athletes who routinely train and perform at intensities near maximum V̇O_2_ max value may experience less ergogenic effect on time-to-exhaustion with probiotics compared to non-elite athletes [11, 16]. Probiotic administration in the non-elite athlete may produce greater effects on physiological responses to exercise such as endurance, perception of muscle effort, and energy metabolism (blood lactate and blood glucose). Non-elite runners may also benefit from probiotic-induced immunomodulatory and gastrointestinal effects that could modulate performance, but this has yet to be determined [17].

### Objectives

The primary objective of this study is to assess the ergogenic effects of a probiotic on high-intensity endurance running performance in non-elite runners. Secondary objectives include assessment of perceived exertion, blood chemistry, immune and stress biomarkers, cold and flu episodes, and gastrointestinal health after the probiotic intervention. We hypothesize that a 6-week probiotic intervention will increase time-to-exhaustion during running and reduce the number of gastrointestinal and cold/flu symptoms compared to the placebo.

### Trial design

This is a randomized, placebo-controlled, double-blind, parallel study design. Allocation was set in a 1:1 ratio (intervention: placebo) for this superiority trial.

## Methods: participants, interventions and outcomes

### Study setting

This trial is being conducted in a sports performance center of a tertiary care medical center, in accordance with the Good Clinical Practice-International Conference on Harmonization guidelines. All study procedures and documents have been approved by the University of Florida Institutional Review Board (18 December 2020, study # IRB202001882). This study is registered as a clinical trial on ClinicalTrials.gov, NCT04588142 (October 19, 2020). SPIRIT reporting guidelines were used in the development of this manuscript [18].

### Eligibility criteria for participants

Participants must meet the following inclusion criteria to be enrolled in the trial: (1) healthy adults between 18 and 45 years old; (2) running or cross-training 3–5 days per week at 45 min to 1.5 h per activity session, and willing to maintain this level of training throughout the study; (3) running ≥24 km per week; (4) willing to discontinue consumption of probiotic supplements and probiotic-fortified products throughout the study; (5) a V̇O_2_ max value in the 60–85th percentile (good-excellent health) range according to American College of Sports Medicine (ACSM) guidelines [19]; (6) willing and able to complete the informed consent from in English.

The exclusion criteria are as follows: (1) any physician-diagnosed diseases that would impact exercise performance or participation, including gastrointestinal disease, heart/cardiopulmonary disease, diabetes, thyroid disease, hypogonadism, hepatorenal disease, musculoskeletal disorder, neuromuscular/neurological disease, autoimmune disease, cancer, peptic ulcers or anemia; (2) professional or elite status; (3) currently smoking (including vaping); (4) positive results on COVID-19 test performed in the last 4 weeks and/or currently experiencing symptoms of COVID-19; (5) pregnancy before or during the study, planning to get pregnant or breastfeeding; (6) severe lactose intolerance and/or allergy to milk, soy, or yeast; and (7) used any antibiotic drug within 4 weeks of randomization. If antibiotic treatment is started while on the study, the participant will not be withdrawn; however, the participant will be asked to take the antibiotic and the study supplement 6 h apart.

### Recruitment

Recruitment for this study will begin in February 2021 and is estimated to finish in February 2022. Potential participants will be recruited via flyers, posters, email announcements, social media announcements, word-of-mouth, and sharing the opportunity at local running group meetings. Interested participants will complete a self-screening questionnaire and then study coordinators will contact the potential participant via phone or email.

### Informed consent

All participants will provide written informed consent after clear explanation of the trial by qualified, experienced members of the research team (study coordinators) prior to any trial-related procedures. Participants will be consenting to all trial procedures and potential future studies that will use their deidentified stool samples. All consenting procedures will be performed in a private area in the UF Health Sports Performance Center. The study coordinator will review the entire form and answer any questions from the potential participant.

### Probiotic intervention

The comparators were chosen to provide either active probiotic or inert placebo. The probiotic (5×10^9^ CFU/capsule) and corresponding placebo were provided by Lallemand Health Solutions Inc. This dosage was selected to determine probiotic efficacy in this athletic population. Placebo capsules contain the same excipients, namely ascorbic acid, magnesium stearate, and potato starch, without the probiotic. The probiotic and placebo capsules are sensorially identical (same smell, taste, and look) which allows for allocation concealment. Participants will receive all study capsules (probiotic or placebo) at the randomization visit and will be instructed to consume one capsule daily with a meal for 6 weeks. Criteria for discontinuing the intervention will be the occurrence of any clinical adverse event (AE) related to the intervention, laboratory abnormality, or other medical conditions (e.g., pregnancy) or situations such that continued participation in the study would not be in the best interest of the participant.

### Compliance with intervention

Study monitoring will be performed by the study sponsor through monthly data monitoring forms. Daily and weekly questionnaires will assess participant compliance with consumption of the study supplement. The daily and weekly questionnaires will be administered electronically via Qualtrics Survey Software (SAP Software Solutions). Study coordinators will monitor daily questionnaires for completion and a second reminder will be sent to participants who do not complete daily questionnaires by 6PM each day. Missed daily questionnaires will be interpreted as if no capsule was taken that day, and the participant will be instructed to consume two capsules the following day. Compliance will be calculated as the number of capsules consumed divided by the number the participant was expected to consume. Noncompliance will be considered as <80% consumed. Stool samples collected before and after the intervention will be used to assess the presence of the probiotic strain and confirm compliance.

### Randomization, sequence generation, concealment, and blinding

The randomization scheme using pre-defined blocks will be generated using a random number generator by laboratory personnel unrelated to the study. Four codes will be used for the placebo and probiotic to preserve blinding in case an adverse event requires unblinding. Allocation will be done in a 1:1 ratio using sealed, opaque envelopes that will also conceal the randomization sequence. Participants will be stratified by sex and randomized on-site by trained staff into two parallel arms (*n*=16/arm) to receive either the probiotic or placebo. Participants and study personnel on-site (Principal Investigator and co-Investigators, research coordinator, and assistants) and off-site personnel involved in the study (project manager, laboratory manager, and technicians) will remain blinded throughout the trial. Upon study completion, the study sponsor will reveal which codes are paired. However, all research personnel related to the study will remain fully blinded until all data analyses are complete. Once all analyses are complete, all study personnel will meet for unblinding.

### Primary and secondary outcomes

Primary and secondary outcomes are summarized in Table 1. The primary outcome measure is the difference in time-to-exhaustion during the endurance treadmill test (run at the HR corresponding to 85% of V̇O_2_ max) between the probiotic and placebo groups after a 6-week intervention. Changes will be adjusted for corresponding baseline time-to-exhaustion values. Longer time to exhaustion is a desired outcome for runners and offers a performance advantage in a competitive environment.

**Table 1 Tab1:** Descriptions of the study outcome measures

Outcome	Description
Primary	
Time-to-exhaustion during treadmill endurance run	During an endurance treadmill run performed at the heart rate (HR) corresponding to 85% maximal rate of oxygen consumption (V̇O_2_max), the participant will run until voluntary time to exhaustion (reflected by meeting 2 out of 3 criteria: respiratory quotient ratio (VCO_2_/VO_2_) ≥ 1.1; HR reaches a minimum of 85% of age-predicted maximal HR (220 minus age); rating of 17 on the 6 to 20 point Borg Rating of Perceived Exertion scale (BRPE).
Secondary	
Blood chemistries	Capillary blood samples will be collected before, during, and after the treadmill endurance test to determine concentrations of glucose and lactate. These metabolites will be quantified using commercial, handheld colorimetric devices (ContourNext EZ glucose meter, LactatePlus lactate meter).
Body composition	This variable will be assessed using the scale (to assess weight) and BOD POD®, a body composition measuring device that measures fat mass and lean muscle mass. Coefficients of variation are 12%, and ICC are 0.9 [20].
Borg Rating of Perceived Exertion Scale (BRPE):	Exertion is a subjective estimate of exercising intensity. This self-reported instrument assesses effort and fatigue due to physical work [21]. Ratings range from 6=no muscle effort to 20=maximal muscle effort possible, cannot work any harder.
Bristol Stool Scale (BSFS):	Is a 7-point, self-rated scale of changes in stool form (hardness, shape, water content) that corresponds to intestinal transit time (*r*=−0.65) [22]. This tool is being used to monitor responses to the intervention and is supported for use in gastrointestinal research.
Daily Questionnaire:	Is a self-administered, online, daily questionnaire. The items include muscle soreness, consumption of supplements other than the study supplement, and compliance. There are also questions on cold/flu symptoms (used in previous trials) [23].
Gastrointestinal Severity Rating Scale (GSRS):	This assesses the severity of gastrointestinal symptoms. The GSRS scores 15 items evaluated in a 7-point Likert scale (1–*No discomfort* to 7–*Very severe discomfort*). The questionnaire is composed of a total score (sum of scores from all 15 items) and five subscales: abdominal pain (questions regarding abdominal pain, hunger pains, and nausea), constipation syndrome (questions regarding constipation, hard stools, feeling of incomplete evacuation), diarrhea syndrome (questions regarding diarrhea, loose stools, urgent need for defecation), indigestion syndrome (questions regarding rumbling, bloating, burping, gas) and reflux syndrome (questions regarding heartburn, acid regurgitation). Scores for each question are averaged to provide the sub-scale score. Reliability of the subscales is relatively good, with the Cronbach’s alpha ranging 0.61 to 0.83 [24].
Digestion-associated Quality of Life Questionnaire (DQLQ):	The impact of GI symptoms on quality of life among healthy adults is measured with this survey [25]. The DQLQ reflects the sum from 9 statements scored on a 10-point Likert scale (0 = *never* to 1 = *always*). This questionnaire has high convergent validity with GSRS-QOL scores r=0.54. Test-retest reliability between the DQLQ and GSRS were reported as ICC=0.89 [25].
Immune and Stress Biomarkers:	Salivary levels of secretory immunoglobulin A (sIgA), alpha-amylase, and cortisol are biomarkers of systemic immune function and stress. Biomarkers will be quantified using ELISA methods using commercial kits.
Covariates	
Short Healthy Eating Index (sHEI):	This instrument is designed to assess nutrient intake [26]. This is a self-report instrument designed to assess quality of diet relative to the American Dietary Guidelines. This validated instrument assesses 22 items to characterize dietary intake and yields a score between 0 and 100. The higher the score, the more the dietary quality aligns with the American Dietary Guidelines.
Fiber Screener:	This is a free-access tool created by NutritionQuest [27]. The range of possible results is between 15 g of fiber daily to 54 g of fiber daily. Higher grams of fiber consumed daily is associated with better general health. Validity was assessed using Spearman rank-order correlation coefficients between this short food screener and a full-length Food Frequency Questionnaire. Fruits and vegetable correlations were reported as *r* =0.71.
Behavioral Regulation in Exercise Questionnaire (BREQ-3):	This assesses the motivation for exercising. The questionnaire operationalizes motivation into six weighted scales: external regulation, introjected regulation, identified regulation, intrinsic regulation, integrated regulation and amotivation—which count with four items. Positive scores are associated to intrinsic motivation, which is better on the long term for exercising, while negative results are associated to extrinsic and lack of motivation. The questionnaire has demonstrated factorial reliability that was assessed using confirmatory factor analysis with LISREL 8.51 [28].
Stool Biochemistries	Probiotic strain recovery will be performed on stool samples before and after the intervention to support associations between outcomes and the probiotic. DNA will be extracted from homogenized stool samples using the ZymoBIOMICS 96 MagBead DNA kit (Zymo Research, cat# D4308). The absolute quantification is achieved using the CFX384 Touch Real-Time qPCR Detection System (Bio-Rad Laboratories) according to previously described methods [29] using specific forward and reverse primers.

The secondary outcomes, which will compare probiotic and placebo groups while adjusting for the corresponding baseline values, are as follows: (A) Borg Rating of Perceived Exertion (BRPE) [21] at peak lactate threshold during the endurance treadmill test (represents greater perceived tolerance to running workload); (B) exercise-induced changes in blood chemistry, specifically glucose concentrations and lactate threshold during the endurance treadmill test (reflects fuel use patterns during running); (C) biomarkers of stress (salivary cortisol and alpha-amylase) and biomarkers of immune activity (salivary secretory immunoglobulin A; sIgA); (D) cold/flu symptoms (severity, duration and number of episodes) as self-reported on the daily questionnaire [23]; (E) gastrointestinal function and discomfort as assessed by the weekly administration of the Gastrointestinal Symptoms Rating Scale (GSRS) [24] and (Digestion-associated Quality of Life Questionnaire (DQLQ) [25] and stool frequency and consistency (Bristol Stool Scale; BSFS) [22] as self-reported on the daily questionnaire; and (F) change in body composition (% fat, % fat-free mass, fat-free mass, fat mass, and body mass) from baseline between the probiotic and placebo groups.

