**Fig. 2 Fig2:**
[figure not shown]
Treadmill endurance running test protocol for visits 3 (baseline) and 4 (final, 6 weeks post-intervention)

The treadmill endurance exercise test will be conducted at a level grade (Fig. 2). Participants will be asked to wear a HR monitor (Polar H10; Polar Inc; Dayton OH) throughout the test. The test consists of a 6-min warm-up period during which the speed of the treadmill will be increased until the participant achieves a HR of 85% of V̇O_2_ max and will continue at this speed until exhaustion or the participant asks to stop. Time-to-exhaustion is defined as meeting two out of three criteria: RQ ratio (VCO_2_/VO_2_) ≥ 1.1; HR reaches a minimum of 85% of age-predicted maximal HR (220 minus age); rating of 17 on the BRPE scale. Participants then remain seated for a recovery period where HR and blood pressure recover and are measured for safety before clearing participants to leave the testing area.

Throughout the test, HR, blood pressure, angina, dyspnea, and BRPE will be collected while finger prick blood samples will be used to measure glucose (Contour®Next EZ; blood glucose monitor; Parsippany, NJ) and lactate (Lactate Plus, Nova Biomedical; Waltham, MA) levels. These measurements will be collected at rest, 5 min into the treadmill test, then every 2–3 min until the participant reaches exhaustion, and once more 3 min after completion of the test.

After this visit, participants will begin their probiotic intervention and continue their daily and weekly questionnaires.

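### Secondary outcomes A and B rest on a lactate threshold that a constant-speed run cannot supply; both should be restated as values at a common elapsed time

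*Protocol article*

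**What the plan says.** In the protocol article, under Primary and secondary outcomes, outcome A is the Borg rating "at peak lactate threshold during the endurance treadmill test". Outcome B is the exercise-induced change in blood chemistry, "specifically glucose concentrations and lactate threshold during the endurance treadmill test". Both are to be compared between groups with adjustment for the corresponding baseline value. The article defines neither threshold term.

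The run itself is described under Visit 3, around Fig. 2:

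- **Grade:** "The treadmill endurance exercise test will be conducted at a level grade".
- **Speed:** "The test consists of a 6-min warm-up period during which the speed of the treadmill will be increased" to reach the target heart rate, after which the runner "will continue at this speed until exhaustion or the participant asks to stop".
- **Sampling:** at rest, at 5 min, "then every 2–3 min until the participant reaches exhaustion", and once more 3 min after the end.
- **Exhaustion:** any two of respiratory quotient at least 1.1, heart rate at least 85% of the age-predicted maximum, and a Borg rating of 17.

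Visit 4 repeats these procedures. Table 1 states that the capillary samples are used to determine glucose and lactate concentrations. It does not mention a threshold. The section on V̇O2 max testing describes the trial's only graded test, done once at Visit 2, and lists no lactate measurement in it. Statistical methods applies a baseline-adjusted linear model to blood chemistries and perceived exertion, which needs a defined value at each visit.

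**The concern.** A lactate threshold is the workload at which lactate begins to rise, so estimating one takes lactate readings at several workloads. The endurance run has one sustained workload. Two named secondary outcomes then depend on a quantity the test does not produce, and whoever analyses the trial will have to substitute something else. If that choice is made late, it is a choice among several lactate and Borg summaries in a trial of 32 people.

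The most natural substitute, peak or end-of-run lactate with the Borg rating at that moment, has two weaknesses. The Borg rating helps to decide when the run ends, so its value at the end is partly set by the rule. The moment of measurement also moves with time-to-exhaustion, so a group difference in end-of-run values would mix an effect on physiology with an effect on running time.

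**Working it through.** No stated figure depends on this point. The sample size reproduces: 2.5/2.0 gives a standardised difference of 1.25, a two-sided t-test at 0.05 has power 0.796 with 11 per arm and 0.833 with 12, and 24/(1 − 0.20) = 30. The rest is mainly a comparison of passages.

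**1. Workloads at which lactate is sampled.** Speed rises only between 0 and 6 min, and grade never changes. The exercise samples fall at 5 min, then at 5 + 2 = 7 to 5 + 3 = 8 min, then at 9 to 11 min, and so on. One exercise sample lies inside the warm-up and every later one is at the held speed. If the 5-min clock instead started after the warm-up, no exercise sample would lie in the rising part. Either way there is no graded series. The phrase in the outcomes section about running at the heart rate for 85% of V̇O2 max still describes one target intensity.

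**2. Could another test supply it?** The V̇O2 max test is graded in 3-min stages, but no lactate sampling is described there. Since it is not repeated after the intervention, it could not give a final-visit value in any case.

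**3. Borg rating if the end of the run is meant.** The heart-rate criterion is 0.85 × (220 − age): 171.7 bpm at age 18, 161.5 at 30 and 148.75 at 45. The article gives no individual heart rates. Assume that the target heart rate already meets this criterion and that runners stop exactly when the rule is met. The run then ends at the first of respiratory quotient 1.1 or Borg 17. Let a share p stop on respiratory quotient first, with Borg spread evenly over a lower range of mean m and variance v. Then

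- mean = 17 − p(17 − m)
- variance = p·v + p(1 − p)(17 − m)²

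| p | Borg range when stopped on respiratory quotient | Mean | SD |
|---|---|---|---|
| 0 | – | 17.0 | 0 |
| 0.25 | 15–16 (m = 15.5, v = 0.25) | 17 − 0.25 × 1.5 = 16.6 | √(0.0625 + 0.4219) = 0.70 |
| 0.50 | 15–16 | 17 − 0.50 × 1.5 = 16.3 | √(0.125 + 0.5625) = 0.83 |
| 0.75 | 13–16 (m = 14.5, v = 1.25) | 17 − 0.75 × 2.5 = 15.1 | √(0.9375 + 1.1719) = 1.45 |

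The shares and ranges are assumptions. They show compression, and they also show that the rating need not be constant.

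**4. Timing if the end of the run is meant.** The planning difference in time-to-exhaustion is 2.5 min. Against a sampling interval of 2 to 3 min that is 2.5/3 = 0.8 to 2.5/2 = 1.25 intervals. If the planned effect occurs, end-of-run values in the probiotic arm are taken about one sampling interval later on average.

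**The case against.** The best defence is that this is a condensed article. The full protocol or analysis plan may define the measure, and Fig. 2, which shows the test, is not reproduced in the text available. Outcome B is introduced as change in blood chemistry, and lactate concentrations are collected and can be modelled. That last point stands: only the threshold is unobtainable, and a reader who concludes that outcome B has no usable lactate data goes too far. The appeal to a fuller document helps less. A later definition cannot recover a threshold from workloads that were not run, so it would have to replace the outcome with something else, such as a concentration at a set time.

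Several stronger readings are tempting and are not supported:

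- **That Borg is fixed near 17, or confined to 17–20, so outcome A cannot show a difference.** Exhaustion is any two of three criteria and a runner may ask to stop. A run can end on respiratory quotient and heart rate with Borg below 17, or with Borg above 17. Reading outcome A as the rating at peak lactate is also an interpretation, because the article says peak lactate threshold.
- **That longer runs necessarily show higher lactate.** The article gives no lactate time course, so this is plausible but undocumented.
- **That the sampling schedules conflict.** The abstract has "finger sticks assessing capillary blood glucose and lactate concentrations will be collected every 3 min", which fits within the 2–3 min interval given under Visit 3.

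**Conclusion.** The concern holds in limited form. As described, the endurance run cannot yield the lactate threshold that outcomes A and B name, and the outcomes section does not match Table 1. This is a mismatch between outcome and test, not just an omitted detail, and it applies to all 32 planned runners at both visits. Under the peak or end-of-run reading, the Borg rating is partly constrained by the stopping rule (illustrative means 15.1 to 17.0, SD 0 to 1.45, under the assumptions above). Its timing is also linked to the primary outcome.

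The conclusion rests on the usual meaning of a lactate threshold as a workload, and on the text's description of the test being complete in the absence of the figure. Two secondary outcomes are affected. The primary outcome, its analysis and the sample size are not. The outcomes should be redefined while the analysis team is still blinded.

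**What to change.** Bring the outcomes section into line with Table 1. Replace both threshold terms with lactate concentration, glucose concentration and Borg rating at one stated elapsed time, with these conditions:

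- The time lies after the 6-min warm-up. The 5-min sample does not qualify, because speed may still be rising then; the first possible sample on the existing schedule is at 7 to 8 min.
- Nearly all runners reach it. The article gives no distribution of run times, so choose it from baseline runs pooled over arms and without knowledge of allocation.
- It is taken at the same nominal time at both visits, and the actual time is recorded.
- The comparison adjusts for the same-time baseline value and for sex.
- Treadmill speed is reported by visit and arm. Speed is set by heart rate and the article does not hold it equal across visits, so the same elapsed time need not mean the same workload.
- Peak and end-of-run values are reported descriptively.

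The cost is small but goes beyond wording. Samples are already being taken, but one sampling time must be held fixed within the 2–3 min schedule, and the trial is already enrolling, so runs completed earlier may have a sample slightly off that time. Later samples drop out of the formal comparison.
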